### Definitions of symptomatic and asymptomatic patient

- Acute symptomatic patient: Positive PCR. Manifests any of the symptoms compatible with COVID-19 at the time of the study or analysis or during admission. These symptoms may vary based on new findings.
- Symptomatic patient: Patients with symptoms before 14 days of delivery, even if they no longer have symptoms at the time of delivery.
- Asymptomatic patient: Positive PCR. No symptoms compatible with COVID-19 were observed at the time of the study or analysis.
- Ex-symptomatic or cured patient: Positive or negative PCR. The patient was symptomatic (PCR+) more than 14 days before delivery and no longer has any of the symptoms compatible with COVID-19 at the time of the study or analysis. Patient can be IgM positive or negative, but shall be IgG+ if serology is available
- Symptomatic patient with sequelae: Positive or negative PCR. The patient was symptomatic (PCR+) and has any of the sequelae recognized after COVID-19 at the time of data analysis. These sequelae may vary based on new findings.

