### Secondary objectives

1. Establish incidence of COVID-19 infections diagnosed in pregnant women in the Spanish population.
2. Determine the variables that are associated with more maternal and neonatal morbidity.
3. Determine if there is vertical transmission.
4. Evaluate the risk of SARS-CoV-2 infection during pregnancy.
5. Characterize the clinical course of SARS-CoV-2 infection during pregnancy (for example, severity of maternal symptoms, distribution of gestational age at onset, ICU admission, mechanical ventilation, death).
6. Quantify the risk of adverse pregnancy outcomes (e.g., miscarriage, stillbirth, growth restriction) and neonatal outcomes (e.g., NICU, prematurity, death, birth defects).
7. Identify additional risk factors and risk modifiers (e.g., symptomatic infection, SARS-CoV-2 positive amniotic fluid, co-infections).

8. Develop a responsive data collection tool across a network of healthcare facilities to ensure rapid assessment of risks associated with future emerging pathogens and to help develop guidelines on this disease.
9. Strengthen capacity-building in data exchange against emerging pathogens.

The collected dataset will allow a comprehensive characterization of the risks associated with SARS-CoV-2 infection in pregnancy. In the future, the developed structure will allow a rapid assessment of the risks linked to future emerging pathogens.

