#### Evaluation 14 days after delivery, N

|                                                   |                                 |
|---------------------------------------------------|---------------------------------|
|                                                   |                                 |
| Symptomatology, n (%)                      | Showing COVID-19 symptoms       |
|                                                   | Asymptomatic                    |
| COVID-19 symptoms                          |                                 |
| Mild symptoms (Symptoms reported at birth) | Cough                           |
|                                                   | Fever                           |
|                                                   | Dyspnoea                        |
|                                                   | New olfactory or taste disorder |
|                                                   | Fatigue/malaise                 |
|                                                   | Altered consciousness           |
|                                                   | Headache                        |
|                                                   | Nausea/vomiting                 |
|                                                   | Diarrhoea                       |
| Mild-moderate pneumonia                    |                                 |
| Severe pneumonia                           |                                 |
| Septic shock/maternal mortality            |                                 |

The rest of the variables are defined in appendix 5

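### The Asymptomatic definition ignores past symptoms and the 14-day window is ambiguous, so the symptom-status groups overlap for PCR-positive women who have recovered

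*Protocol*

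**What the plan says.** The Protocol section *Definitions of symptomatic and asymptomatic patient* lists five groups: acute symptomatic, symptomatic, asymptomatic, ex-symptomatic or cured, and symptomatic with sequelae. It gives no order of precedence and does not say that a woman belongs to only one. Three of the rules matter most here:

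- "Symptomatic patient: Patients with symptoms before 14 days of delivery, even if they no longer have symptoms at the time of delivery". This rule carries no PCR condition and keeps women who have recovered.
- "Asymptomatic patient: Positive PCR. No symptoms compatible with COVID-19 were observed at the time of the study or analysis". This rule says nothing about earlier symptoms.
- "Ex-symptomatic or cured patient: Positive or negative PCR", with the condition "The patient was symptomatic (PCR+) more than 14 days before delivery and no longer has any of the symptoms compatible with COVID-19". PCR-positive women are admitted, so PCR status does not separate this group from Asymptomatic.

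Symptom status is then used. Substudy 1 lists symptomatology with two levels (symptoms, asymptomatic) among its primary variables under *Maternal characteristics*, and again in the evaluation 14 days after delivery. *Secondary objectives* includes "Identify additional risk factors and risk modifiers (e.g., symptomatic infection, SARS-CoV-2 positive amniotic fluid, co-infections", and the objectives of Substudies 1 and 2 repeat it. No section says how the five groups map onto the two levels.

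**The concern.** One rule looks back in time and another looks only at the present, and nothing decides between them. Recovered women are not a rare edge case. Infection qualifies at any time in pregnancy (*Study design*), and Substudy 1 records the interval from diagnosis to delivery. With 100 sites (*Overall sample size*) and one data collector at each (*Data quality assurance plan*), two sites can both follow the text and code the same woman differently.

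At stake are the reported symptomatic/asymptomatic split in Substudy 1 and any later analysis that treats symptomatic infection as a risk factor or modifier.

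**Working it through.** The protocol states no figure on this point. The check is therefore logical, followed by an illustration on assumed numbers.

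**1. Applying the rules.** Take a PCR-positive woman without sequelae, with IgG positive or not measured, whose symptoms resolved before delivery. Three inputs come from the wording or are assumed:

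- three symptom histories, in days before delivery (assumed): onset 10 and resolved 3; onset 20 and resolved 10; onset 40 and resolved 30;
- two PCR dates (assumed): at onset, or at delivery;
- two readings of the 14-day phrase (within 14 days; more than 14 days before) and three readings of the reference time (PCR test, delivery, data analysis).

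That gives 3 × 2 × 2 × 3 = 36 combinations. With status read at delivery, the result is the same for both PCR dates:

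| History | Phrase read as within 14 days | Phrase read as more than 14 days before |
|---|---|---|
| 10 / 3 | Symptomatic and Asymptomatic | Asymptomatic only |
| 20 / 10 | Symptomatic, Asymptomatic and Ex-symptomatic | Symptomatic, Asymptomatic and Ex-symptomatic |
| 40 / 30 | Asymptomatic and Ex-symptomatic | Symptomatic, Asymptomatic and Ex-symptomatic |

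Over all 36 combinations:

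- 14 give two groups, 15 give three and 7 give one, so 14 + 15 = 29 overlap.
- In 20 she is both Symptomatic and Asymptomatic.
- Four of the 29 are only Acute symptomatic plus Symptomatic, which does not disturb a two-level split. In the other 29 − 4 = 25, Asymptomatic coincides with a group that records past symptoms.
- Of the 7 single-group results, 6 are the 10/3 history under the more-than-14-days reading. In 5 of those 6 a woman with symptoms in the last two weeks is simply Asymptomatic.
- No combination of readings gives one group for all three histories.

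The count takes the PCR+ note in the Ex-symptomatic rule as met by a positive test on either date. If the test had to be positive while she was symptomatic, 3 combinations (40/30, tested at delivery, within-14-days reading) become Asymptomatic only. The overlap count is then 29 − 3 = 26, and the 20 that are both Symptomatic and Asymptomatic do not change.

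**2. What coding can do to an estimate.** Assume 1,000 cases: 400 ever symptomatic with outcome risk 20% (80 events) and 600 never symptomatic with risk 10% (60 events). Ever versus never: risk ratio 2.0, OR = (0.20/0.80)/(0.10/0.90) = 2.25. Let 200 of the 400 have recovered and be coded asymptomatic. The symptomatic share falls from 400/1,000 = 40% to 200/1,000 = 20%.

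- Recovered women carry the same 20% risk: risk in those coded asymptomatic = (60 + 40)/800 = 12.5%; risk ratio 20/12.5 = 1.6; OR = (0.20/0.80)/(0.125/0.875) = 1.75.
- Same totals, but recovered women carry 10% (20 events) and current ones 30% (60 events): risk in those coded asymptomatic = (60 + 20)/800 = 10%; risk ratio 30/10 = 3.0; OR = (0.30/0.70)/(0.10/0.90) = 3.86.

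Under the equal-risk assumption, 100 or 300 recovered women give OR = 0.25/(80/620) = 1.94 or 0.25/(120/780) = 1.63. That range varies only the number recovered and says nothing about direction.

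**The case against.** The strongest reply is that little depends on these groups. The statistics sections of all four substudies test association with infection, which is defined by PCR whatever the symptoms, and Substudy 3 is interested only in the COVID factor. Symptomatology is a count-and-percentage row, and symptomatic infection appears only as an example within an objective. This stands. A reader might infer that a planned symptomatic-versus-asymptomatic test is left undefined, but the protocol names no such test.

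Four further points need weighing:

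- **All three groups at 20 days.** A reader might infer that a woman whose symptoms ended 20 days before delivery fits three groups. That needs the less natural reading of the 14-day phrase. Beside the Ex-symptomatic rule, within 14 days is the more natural sense, and on it she fits at most two. A woman with onset at 20 and resolution at 10 days does fit three when status is read at delivery.
- **Bias towards the null.** A reader might infer this. It holds only if recovered women keep a risk close to that of currently symptomatic women, and the documents give no such figure.
- **Symptom tables.** A reader might take the row label "Mild symptoms (Symptoms reported at birth" to mean that Substudy 2 describes the whole course of infection from a snapshot at birth. Appendix 2 lists diagnosis, admission, emergency and follow-up forms, and Appendix 5 holds the remaining variables, so the documents do not support that.
- **Appendix 5.** It is a separate file, not shown, and may define the data field. It could settle the coding in practice, but would not remove the contradiction in the protocol's own text.

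**Conclusion.** The point holds as a defect in definitions that the protocol itself fixes. Asymptomatic has no condition on past symptoms, the reference time is not tied to an event, and the 14-day phrase has two meanings. Under the natural within-14-days reading, with status read at delivery, recently recovered women meet contradictory rules; under the other reading they usually fall into Asymptomatic.

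The effect is on the Substudy 1 symptomatic share and on any analysis of symptomatic infection as a risk modifier. Its size cannot be taken from the documents. In the illustration the share halves, and an OR of 2.25 moves to 1.75 or 3.86; all of those inputs are assumed. The comparison of PCR-positive with PCR-negative women and the WHO severity classes are untouched, so this should be corrected but does not threaten the main contrast.

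**What to change.** - Set one reference time point for symptom status, and name it in every rule and table that uses it.
- Define Asymptomatic as PCR-positive with no compatible symptoms from the earlier of symptom onset and first positive PCR up to that point. Symptoms that resolved before a screening test at delivery then count.
- Reword the 14-day phrase so that the Symptomatic and Ex-symptomatic windows are complementary and keyed to the same date, for example the last day with symptoms. On that basis, with delivery as the reference time, the 10/3 and 20/10 histories are Symptomatic only and the 40/30 history is Ex-symptomatic only.
- Make all five groups exclusive or give an order of precedence. Include acute symptomatic, sequelae, and symptoms that start after delivery, since postpartum cases are within the primary objective.
- State how the five groups map onto the two-level symptomatology variable, at birth and at 14 days.

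The cost is a change of wording and of derivation code. The protocol names a COVID-19 diagnosis form but does not show its fields, and the substudy tables list only a diagnosis date. Use onset and resolution dates where the forms collect them; otherwise use an ever/never symptom field, which supports the two-level variable but not the 14-day windows.

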## Study population and selection criteria

For the characterization of the clinical course of SARS-CoV-2 infection during pregnancy, the pre-study sample size calculation has not been carried out, as registry-based studies generally tend to be comprehensive without involving hypotheses.

Patients eligible for follow-up of target population will be any pregnant woman who is suspected or needs to be ruled out as having a SARS-CoV-2 infection at any time during pregnancy with positive test results for SARS-CoV-2 by PCR.

Information regarding each pregnant woman's demographic characteristics, comorbidities and current obstetric history was extracted from the medical history and the patient interview; subsequently, age and race were categorized according to the classification used by the Center for Disease Control and Prevention (CDC) (17).

For the selection of the control group to be collected in the same database, patients with a negative COVID-19 delivery diagnosed by PCR screening at delivery, or less than 3 days before, were considered.

### Exclusion criteria

Pregnant women under the following conditions will be excluded from the registry:

- Inability to give informed consent in the absence of a legal representative.
- If, in the opinion of the researcher, findings in the physical examination, anomalies in the results of the laboratory tests or other medical, social or psychosocial factors could have a negative influence.
- Loss of follow-up data prior to 6 weeks postpartum.

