## Study design

Prospective observational registry study of pregnant women with suspected SARS-CoV-2 infection at any time during pregnancy with positive test results for SARS-CoV-2.

A specific database will be developed, which will include the baseline characteristics of the pregnant women, aspects related to the course of pregnancy and childbirth, and the new-born. Vertical transmission will be analysed only by means of a nasopharyngeal swab from the new-born before contact with the mother. This registry sets an observation deadline of up to 14 days after birth for the new-born and 6 weeks postpartum for the mother. The registry will be hosted on a secure https server, this server will be physically located at **OBS Covid Spain** of the company ReserArch which has a contract with the Puerta de Hierro-Majadahonda University Hospital Research Foundation.

Recruitment period will be between 1st March 2020 and 1st March 2021.

After that, different sub-analyses will be carried out with the data extracted in the registry and the secondary objectives will be addressed.

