## Data sources and work plan

### Patient referral sources

If the doctor in charge considers it appropriate to inform the patient about the existence and purpose of this registry, he/she may do so. At this time, consent will be requested so that the information derived from the regular monitoring of these patients is incorporated into the data registry, and that said information can be analysed and disclosed for scientific purposes in accord with the confidentiality provisions of the current legislation.

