### Data collection

Encrypted health-related personal data is collected prospectively using the **OBS Covid Spain** database of the company ReserArch.

The collection of data on each pregnant woman is planned from the diagnosis of a case in a pregnancy up to 6 weeks after delivery and up to 14 days postpartum in the case of the new-born, based on a manual prepared for the collection of data and for the investigator.

Hospitals enrol their pregnant patients on an ongoing basis, and the information is collected and stored anonymously in two separate phases: the first phase, during the inclusion period that occurs at the time of the SARS-CoV-2 test in the pregnant woman; the second phase, throughout the 2 weeks after birth.

For sites with existing cohorts using methods that comply with registry data collection methods (i.e., systematic inclusion of women screened for SARS-CoV-2 regardless of test results, prospective follow-up, and information

requested as shown in the variables table of appendix 5), the data collected will be entered at the time they join the registry.

Delivery monitoring: the *outcomes* include perinatal and neonatal events, which were collected at the time of delivery and the days immediately afterward. These perinatal events included gestational age, type of delivery, presence of prepartum or premature rupture of membranes before delivery, as well as any medical complications (thromboembolic events, admission to ICU, maternal death) and obstetric complications (hemorrhagic events and hypertensive disorders), while neonatal events included the 5-minute Apgar score, the pH of the umbilical artery and possible complications such as admission to the NICU and neonatal death in the follow-up period or intrauterine foetal death. The definitions of obstetric pathology follow the international criteria of the ACOG and RCOG (18-21).

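### Requiring complete data to 6 weeks postpartum, plus an open-ended discretionary exclusion, removes women with recorded outcomes and can bias the registry's risks by an unknown amount

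*Protocol*

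**What the plan says.** The Exclusion criteria open with "Pregnant women under the following conditions will be excluded from the registry", so they act on the registry itself and not on one analysis. Two of the three matter here.

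- The last criterion is "Loss of follow-up data prior to 6 weeks postpartum".
- The second is discretionary. It covers abnormal examination or laboratory results, and wider health or social circumstances, that as the researcher sees it "could have a negative influence". The object of that influence is not named and no objective threshold is given.

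On follow-up, Study design sets an "observation deadline of up to 14 days after birth for the new-born and 6 weeks postpartum for the mother". Data collection says the same, but later on describes two collection phases, of which the last is "the second phase, throughout the 2 weeks after birth". It also says that perinatal and neonatal events are recorded at delivery and in the days just after. These include gestational age, type of delivery, ICU admission, NICU admission, Apgar score and intrauterine death. Follow-up after delivery is by telephone and by consulting the medical history.

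The Abstract and the Rationale both say that the registry should yield a large data set free of bias. The Secondary objectives include the risks of adverse pregnancy and neonatal outcomes and the severity of maternal disease, with ICU admission, ventilation and death. The Statistics section of Substudy 3 makes the odds ratio for COVID the only quantity of interest.

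**The concern.** An exclusion criterion should be decidable at entry. Completeness at 6 weeks is known only months after a woman diagnosed early in pregnancy has been enrolled, and weeks after her delivery outcomes are on file. Applied as written, the rule discards known outcomes because a different, later item is missing. It also makes every reported risk conditional on having completed follow-up.

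Maternal death is the sharpest case. It is an outcome of interest, yet it ends follow-up. If it falls before 6 weeks, the text does not say whether the woman counts as a death or as a loss.

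The discretionary criterion raises a related problem. In an observational registry that adds no tests, abnormal examination or laboratory findings may be markers of the severe disease that the registry sets out to describe. The wording permits removal on those grounds, although it does not say that this is the intention.

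At stake are the absolute risks, and the Substudy 3 odds ratios if outcome-related exclusion differs between cases and controls. Loss rates may well differ between the groups. Under Data collection a case is followed from diagnosis, at any time in pregnancy, whereas a control is identified at delivery or less than 3 days before. That makes different loss plausible. It does not show that loss is related to outcome.

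**Working it through.** The plan has no figure of its own to reproduce: it gives no loss rate, no exclusion rate and no outcome risk. **Every input below is an assumption.**

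**1. Which outcomes are already known when the rule bites**

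| Item | Complete by | Needs 6 weeks? |
|---|---|---|
| Delivery outcomes | delivery and the days after | no |
| Neonatal follow-up | 14 days | no |
| Late maternal complications | 6 weeks | yes |

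Only the last row needs the 6-week data, but the rule removes all three.

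**2. Effect on the Substudy 3 odds ratio when the truth is no effect**

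Let p be the true risk, L the proportion lost, and k the risk in lost women relative to retained women. Then p = (1 − L)q + Lkq, so the risk in retained women is q = p / (1 − L + Lk). Take p = 10% in both groups.

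- Loss 15% in cases, 5% in controls, k = 2: cases 0.10/1.15 = 8.70%; controls 0.10/1.05 = 9.52%. OR = (0.0870/0.9130) / (0.0952/0.9048) = 0.905.
- Same losses, k = 3: 0.10/1.30 = 7.69% v 0.10/1.10 = 9.09%; OR 0.833.
- Losses reversed (5% v 15%), k = 2: OR 1/0.905 = 1.105.
- 15% v 5%, lost women at half the risk (k = 0.5): 0.10/0.925 = 10.81% v 0.10/0.975 = 10.26%; OR 1.06.
- Any losses, k = 1: q = p in both groups; OR 1.00.
- 10% lost in both groups, k = 2: both risks fall to 0.10/1.10 = 9.09%; OR 1.00, but the absolute risk is understated.

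**3. Effect on an absolute risk**

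Let r be the true risk, and a and b the exclusion probabilities with and without the event. Observed risk = r(1 − a) / [r(1 − a) + (1 − r)(1 − b)]. With r = 5%:

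| b (no event) | a (event) | Observed risk |
|---|---|---|
| 10% | 10% | 5.00% |
| 10% | 5% | 5.26% |
| 10% | 20% | 0.040/0.895 = 4.47% |
| 20% | 40% | 0.030/0.790 = 3.80% |
| 20% | 80% | 0.010/0.770 = 1.30% |

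**4. When the odds ratio is safe**

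The observed OR equals the true OR × [(1 − a in cases)(1 − b in controls)] / [(1 − b in cases)(1 − a in controls)]. If a and b are the same in both groups, or if a = b within each group, the factor is 1. If only cases have event-related exclusion (20% v 10%, controls 10% throughout), it is 0.80/0.90 = 0.89. At 40% v 20%, with controls at 20% throughout, it is 0.60/0.80 = 0.75.

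The bias can therefore be sizeable, run either way, or be absent.

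**The case against.** Several stronger readings are tempting, and the document does not support them.

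- **That every risk estimate is biased.** Steps 2 to 4 show conditions under which the bias is zero. Different loss in cases and controls is not enough for the odds ratio: loss that depends on exposure alone leaves it unchanged. Nothing in the protocol shows that loss is related to outcome.
- **That severity is understated.** The discretionary criterion also covers social and psychosocial factors, it can apply to controls, and the text never says what the influence is on. It may have been meant for participation or consent. The fair statement is that the criterion is undefined and permits selection on severity.
- **That a missed call deletes a woman.** The criterion is loss of data, and the medical history is consulted as well as the telephone. This should reduce losses, but it does not withdraw the rule.
- **That maternal collection stops at 2 weeks.** Study design and Data collection, including its text on follow-up after delivery, all give 6 weeks for the mother. The 2-week phase is loose wording.
- **That the exclusions contradict a consecutive design in Substudy 3.** In its Design section that word describes the hospitals' PCR screening, not enrolment.

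Patient referral sources also leaves it to the doctor whether a woman hears of the registry. This limits representativeness, but it is a separate and weaker matter. Substudy 4 has its own random selection.

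What survives all this is the exclusion itself. No other section withdraws it or limits it to late maternal outcomes. Eligibility is fixed in the protocol, so it is not a detail left to an analysis plan.

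**Conclusion.** The point holds in this form. Complete data to 6 weeks is a condition of staying in the registry, so women with full delivery and 14-day neonatal outcomes can be removed, and the status of a maternal death before 6 weeks is unstated. The discretionary criterion is undefined and allows, without stating, selection on features linked to severity. Both conflict with the protocol's own aim of unbiased data.

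The structural defect is certain from the text; the size of its effect is not. The null odds ratios in step 2 (0.83 to 1.11) rest on an assumed 10% risk, assumed losses of 5% to 15% and an assumed relative risk of 0.5 to 3 in lost women. The figures for absolute risk in step 3 are equally hypothetical. They show what the rule could do, not what it has done.

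**What to change.** 1. Delete the loss-to-follow-up exclusion. Analyse delivery and 14-day neonatal outcomes in all enrolled women.
2. Treat missing 6-week maternal outcomes as missing data: censor at last contact and add a sensitivity analysis.
3. State that maternal death is an outcome and not a loss to follow-up.
4. Report completeness at 6 weeks by PCR status.
5. Delete the discretionary examination and laboratory criterion, or limit it to objective reasons unrelated to COVID-19 severity. Report how many women are excluded under it.
6. As a minor point, reconcile the 2-week second phase in Data collection with the 6-week maternal follow-up.

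The cost is amendment wording, some records with incomplete late follow-up, and a short count from each site. If records have already been removed under the present rule, they should be restored where they still exist.
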